##### Explorative outcome measures

The explorative outcome measures are the BDI-II at 15 months, personal and social performance (PSP) [52], health-related quality of life (EQ-5D-3 L) [53], functional impairment (Sheehan Disability Scale (SDS)) [54], quality of life (WHO-five Well-being Index (WHO-5)) [55] and self-efficacy (Personal Control subscale from the revised version of the Illness Perception Questionnaire (IPQ-R) [56] and two subscales from the Chronic Disease Self-Efficacy Scales (SECD-32); and the Obtain Help from Community, Family, Friends Scale and Control/Manage Depression Scale) [57] at 6 and 15 months.

Here, a measure of apathy will also be collected through the Diagnostic Apathia Scale, which consists of six items [58] and side effects from treatment will be measured with the Patient-Rated Inventory of Side Effects (PRISE) which identifies and evaluates the tolerability of symptoms/side effects in nine domains [59].

The PSP measures personal and social functional level in the domains of: socially useful activities (for example, work and education), personal and social relationships, self-care and disturbing and aggressive behaviours on a scale from 1 to 100 with a higher number indicating higher level of function.

The EQ-5D-3 L is a measure of health status in five domains: mobility, self-care, usual activities, pain/discomfort and anxiety/depression and also includes a Visual Analogue Scale from 0 (worst imaginable health status) to 100 (best imaginable health status).

The SDS is a composite of three items designed to measure the extent to which three major domains in the patient’s life are impaired by symptoms, and can be summed into a joint measure of global functional impairment that ranges from 0 (unimpaired) to 30 (highly impaired). The WHO-5 consists of five items that measure the subjective experience of quality of life or psychological wellbeing. Each item is rated on a six-point Likert scale from 0 (not present) to 5 (constantly present).

The IPQ-R has 12 subscales of which the Personal Control subscale consists of six items about one’s own beliefs about the ability to affect the disorder. Each item is rated on a five-point Likert-scale from 1 (disagree very much) to 5 (agree very much).

The two subscales of SECD-32 consist of four and six items about how confident one is in doing certain activities. Each item is rated on a 10-point Likert scale from one (not at all confident) to 10 (very confident).

Information about life-threatening conditions, the use of inpatient and outpatient physical and mental health services and number of days of admission and former treatment is collected through the National Patient Registry which holds information about all patient contacts in the secondary health care system [60].

Medication use is retrieved from the Danish National Prescription Registry which holds information about all sales of medication [61].

Information about deaths is collected through The Danish Register of Causes of Death, which is based on information of all deaths in Denmark since 1943 [62].

Sickness leave, employment and use of other social services will be obtained from the Danish Register for Evaluation of Marginalisation (DREAM), which contains information about contact with the labour market for the entire Danish population [63]. These data are collected at baseline, 6 and 15 months.

At 6 months the patient’s feeling of being supported in their recovery by their primary health care provider (care manager and GP in the intervention group and GP in the control group) is assessed through the INSPIRE questionnaire, which has two sections – one about support (20 items) and one about relationship (seven items) [64].

Participants also rate their general satisfaction with treatment through the CSQ-8 questionnaire [65] together with project-specific questions. The CSQ-8 consists of eight items which are rated on a scale from 0 to 4.

Baseline information, such as former treatment, education and marital status, will be collected through Statistics Denmark, which is the central authority on Danish statistics [66], and the National Patient Registry.

### Data collection

Interview-based assessments such as the GAF-F and the PSP will be conducted through telephone interviews by research assistants who are thoroughly trained in using the instruments. Other data are collected either through self-reported questionnaires or registers (see Fig. 2 for details of sources of data collection). Self-reported questionnaires are completed online or in a paper version. If participants have not completed the questionnaire after 8 days, they will be reminded and, if necessary, they will be contacted in order to collect the missing data. The BAI and BDI-II data can be collected via telephone if it is not possible for the participants to fill them out by themselves. Information about intervention-specific services and treatment will be registered by the care managers and psychiatrists throughout the intervention period.

### Safety measures

The following safety measures are collected:Self-reported anxiety and depression symptoms measured with the BAI [45] and BDI-II [47]Suicidal ideation obtained from the questions concerning suicidality in the MINI baseline eligibility interview [43]Death (natural, accident, suicide, homicide/violence or unknown) obtained from the Danish Register of Causes of Death [62]Life-threatening conditions for reasons other than suicide attempts obtained from the National Patient Registry [60]Number of physical and mental health outpatient services, admissions and inpatient days obtained from the National Patient Registry [60]Number of sickness leave days obtained from the DREAM database [63]

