#### Outcome measures

Participants are interviewed and asked to fill out a questionnaire at baseline, 6 and 15 months’ follow-up. In the following each assessment instrument will be described. See the Standard Protocol Items: Recommendations for Interventional Trials (SPIRIT) figure (Fig. 2) for an overview of time schedule, assessment instruments and source of data collection.

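### The safety list names no measure that identifies non-fatal suicide attempts after baseline, and as written takes suicidal ideation from the baseline interview only

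*Protocol article*

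**What the plan says.** The Safety measures section of the protocol article gives an explicit list of what is collected. Four of its six items bear on suicidality or could contain a suicidal event:

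- Ideation: "Suicidal ideation obtained from the questions concerning suicidality in the MINI baseline eligibility interview".
- Death: "Death (natural, accident, suicide, homicide/violence or unknown) obtained from the Danish Register of Causes of Death".
- Life-threatening conditions: "Life-threatening conditions for reasons other than suicide attempts obtained from the National Patient Registry".
- Service use: "Number of physical and mental health outpatient services, admissions and inpatient days obtained from the National Patient Registry".

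The other two items are BAI and BDI-II symptom scores and days of sickness leave.

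The Explorative outcome measures section draws on the same registry for "Information about life-threatening conditions, the use of inpatient and outpatient physical and mental health services and number of days of admission". There, nothing is excluded from the life-threatening conditions. The same section says that this registry covers every patient contact with secondary care.

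**The concern.** An item worded to exclude suicide attempts normally implies that attempts have an item of their own. Here they do not. The exclusion removes the event from one category and assigns it to no other, and a second section describes the same registry item without it. A reader cannot tell whether attempts count as life-threatening conditions in these trials.

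The ideation item does not fill the gap. A reading taken at the eligibility interview precedes treatment, in patients from whom those at high risk of suicide have been excluded. It describes who entered and cannot show ideation that emerges or resolves later.

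The protocol itself treats suicidality as a safety matter: it lists ideation, names suicide among the causes of death and excludes high-risk patients. At stake is whether the three trials, planned at 364 patients each, can report non-fatal attempts by arm over 15 months. Followed literally, the list does not provide for that.

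**Working it through.** No arithmetic applies and there is no figure in the plan to reproduce. The check takes each safety item and asks whether it is measured after baseline and whether it identifies a suicidal event.

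| Safety item | Measured after baseline? | Identifies a suicidal event? |
|---|---|---|
| BAI and BDI-II | Yes, at 6 and 15 months | Not as described: symptom scores only |
| Suicidal ideation (MINI) | Not as written | At baseline only |
| Death by cause | Yes | Yes, fatal only |
| Life-threatening conditions | Yes | No: attempts are excluded |
| Contacts, admissions, inpatient days | Yes | No: no cause is stated |
| Sickness leave days | Yes | No |

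**Timing of the MINI.** The Baseline eligibility interview section places the MINI at the telephone interview that confirms the diagnosis. The Outcome measures section states: "Participants are interviewed and asked to fill out a questionnaire at baseline, 6 and 15 months". It does not say that the MINI is part of the later interviews. The Data collection section names the GAF-F and the PSP as interview-based assessments, but as examples, so that list is not exhaustive. No sentence states that the suicidality questions are asked again.

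**Attempts in the registry.** The two sections name the same source and the same type of event but differ in scope: Safety measures excludes attempts, Explorative outcome measures does not. Since the registry holds all secondary-care contacts, a hospital-treated attempt is in the data under either description. It would add to the counts of contacts or admissions, where nothing marks it as an attempt.

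**Other instruments.** The PRISE side-effect inventory is an explorative outcome, and the article does not name its nine domains. It cannot be relied on here.

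**Result.** One of the six items identifies a suicidal event after baseline, and only death by suicide. None identifies a non-fatal attempt. As written, ideation is read at one of the three assessment points.

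**The case against.** The strongest reply is that this is a matter of wording and reporting, and that the design does not fail to see the events. Much of that stands:

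- A reader might infer that the trials cannot detect suicidality during treatment at all. The document does not support this, because suicide is a named category of death.
- A reader might infer that non-fatal attempts appear in no safety measure. That is also too strong: hospital-treated attempts fall within the counts of contacts and admissions. They are present but not identified.
- A reader might infer that the plan intends a comparison of the arms on the MINI item, which would be empty. The section says only that the measures are collected, and no such comparison is stated.
- It may be said that the BDI-II, repeated at follow-up and on the safety list, already covers ideation. The article describes it only as a 21-item depression questionnaire and mentions no suicidality item, so the document supports neither that defence nor a remedy built on it.
- The schedule figure (Fig. 2) is not shown, and the article condenses a fuller protocol. A repeat of the MINI questions cannot be ruled out, and registry code lists commonly sit elsewhere.

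The reply does not remove the point. The article is not merely silent: it writes an exclusion into one section that another section lacks, and it ties ideation to the baseline interview. If the MINI questions are in fact repeated, the safety item is worded wrongly and still needs correction.

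**Conclusion.** The point holds in a limited form. As written, no safety measure identifies a non-fatal suicide attempt after baseline, the two sections disagree on whether attempts belong to life-threatening conditions, and ideation is a baseline reading. Suicide deaths are captured, and hospital-treated attempts are held in the planned registry data without a label.

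The size is a gap in harm reporting across three trials with a planned total of 1092 patients. The article gives no attempt rate, so no expected number of events is put on it. The primary outcome, sample size and main analysis are untouched.

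The conclusion on attempts rests on the text of the two sections. The conclusion on ideation rests also on the assumption that the unseen schedule figure shows no follow-up administration of the MINI suicidality questions.

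**What to change.** 1. Reconcile the Safety measures and Explorative outcome measures sections, so that both state the same rule on whether suicide attempts count as life-threatening conditions.
2. Add hospital-treated suicide attempts and self-harm contacts as a separate safety item, from the National Patient Registry extract already planned, reported by arm from baseline to 6 months and from baseline to 15 months. Deleting the exclusion alone would be weaker: attempts would then be merged with other life-threatening conditions and still not be visible.
3. Label the MINI suicidality item as a baseline characteristic. If the questions are repeated at follow-up, correct the wording and state the time points.

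The registry part costs a code list, to be fixed before the groups are unmasked, and one more table row. It needs no new contact with patients. Its limit should be stated with the result: the registry misses attempts that lead to no secondary-care contact, so the item counts hospital-treated events and not all attempts.

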### Training and inter-rater reliability

Trained research assistants will perform the baseline eligibility interviews as well as the objective assessments. Based on sound records, inter-rater reliability is assessed throughout the training and assessment period and discrepancies are discussed with the other raters and at least one of the intervention developers. In the first 3 months, bi-monthly or monthly meetings are held to discuss potential difficulties in rating the objective measures of the PSP scale and the GAF-F scale. Subsequently, reliability ratings related to these measures are performed approximately every 3 months throughout the assessment period.

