The development of a Danish model for collaborative care (the Collabri model) for panic disorder, generalised anxiety disorder and social phobia was completed in 2014 in collaboration between Danish GPs, psychiatrists and researchers. In this paper the protocol (version 2) for three cluster-randomised controlled, superiority trials investigating collaborative care, according to the Collabri model, vs. treatment-as-usual for panic disorder, generalised anxiety disorder and social phobia will be outlined. As we developed specific collaborative care treatment models for each of the three anxiety disorders, and wanted to examine the effect of each of these three collaborative treatment models, we designed three cluster-randomised controlled, superiority trials; but as the trials for each of three anxiety disorders are similar in terms of aim, design and methods, they are jointly presented in this paper. The hypothesis for each of the trials is that treatments according to the Collabri model are more effective than treatment-as-usual.

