### Blinding

The research team (who assess baseline eligibility criteria, collect interviewer-based baseline and follow-up assessments, perform statistical analyses and draw conclusions) are blinded to allocation throughout the entire trial period (from baseline eligibility interview to drawing conclusions). It is not possible to blind GPs, the Collabri team who deliver the intervention, the administrative project team and the participating patients towards intervention allocation. It will be highlighted to them that they cannot reveal their allocation group to the research team. Should the allocation be revealed to the research assistant before assessments (baseline eligibility interview or interviewer-based assessments), another research assistant is allocated. Furthermore, during statistical analyses, the two groups will be coded and anonymised (e.g., X and Y) until final analyses and conclusions have been made.

The referral diagnosis is not revealed to the researchers conducting the baseline eligibility interview until the end of the interview. This makes the assessment of baseline eligibility criteria more objective.

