## Discussion

The design of the trials presents several strengths. The randomisation is carried out externally and is computer based which ensures an adequate allocation sequence and concealment, thus reducing the risk of (cluster) selection bias. In order to further limit the risk of selection bias, data will be analysed according to the intention-to-treat principle and attempts to increase follow-up rates will be made. Also, the trials are randomised at cluster level in an attempt to eliminate the potential risk of contamination otherwise introduced by individual randomisation. This risk could be present where GPs trained in collaborative care principles, and receiving supervision from a project psychiatrist, would not be able to differentiate between intervention and control patients when using their acquired skills and advice from the psychiatrist, which is likely to affect the results, and thereby making it more difficult to detect differences between the intervention and the control group. To ensure that the intervention is provided as intended, we monitor fidelity to the Collabri model at least twice during the intervention period.

The primary outcome is self-reported and patients are not blinded towards allocation, which might result in information bias and possibly overestimation of effects [75]. However, the BAI has been found usable for assessing the severity of anxiety symptoms in patients with anxiety disorders in a general practice setting [76], and other outcome measures will be assessor blinded for allocation; for example, the secondary outcome measure of psychosocial functioning (GAF-F). A limitation, as a result of the cluster-randomisation, may be that patients within a cluster have some similarity and may differ from patients from other clusters. However, sample size calculations including an ICC have been carried out, aiming to reduce this problem. Furthermore, we cannot be sure that all eligible patients are asked to participate by their GP, as patients are not systematically screened for eligibility.

The results of these trials will add to the limited pool of knowledge about collaborative care for patients with anxiety disorders. To our knowledge, they will be the first carried out in a Danish context and the first reporting results for generalised anxiety and social phobia separately.

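### Intervention developers take part in discussing discrepant ratings during the assessment period, which leaves an unclosed blinding gap on GAF-F and PSP

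*Protocol article*

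**What the plan says.** The section Training and inter-rater reliability covers the baseline eligibility interviews and the interviewer-rated outcomes together. Agreement between raters is checked on sound recordings, both in training and while assessments are running. On what follows from a disagreement it says that "discrepancies are discussed with the other raters and at least one of the intervention developers". Early meetings, during an initial 3 months, serve to "discuss potential difficulties in rating the objective measures of the PSP scale and the GAF-F scale". After that, "reliability ratings related to these measures are performed approximately every 3 months throughout the assessment period".

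The Blinding section says that the research team, which does the eligibility interviews, the interviewer-based assessments and the analysis, "are blinded to allocation throughout the entire trial period". It then names those who are not blinded: "It is not possible to blind GPs, the Collabri team who deliver the intervention, the administrative project team and the participating patients towards intervention allocation". Developers of the model appear in neither group. The Background says that the model was developed "in collaboration between Danish GPs, psychiatrists and researchers".

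The Discussion accepts that the primary outcome (BAI) is self-reported by unblinded patients and may overstate the effect. Part of its answer is that "other outcome measures will be assessor blinded for allocation; for example, the secondary outcome measure of psychosocial functioning (GAF-F").

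**The concern.** Of the primary and secondary outcomes, BAI, BDI-II and SCL-90-R are patient questionnaires. GAF-F is the only one rated by an interviewer, so it is the only one for which blinding of the assessor can protect the result, and the Discussion uses it for that purpose.

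The article gives a developer of the tested intervention a standing part in discussing disagreements about ratings while trial data are being collected. This is a stated procedure, not merely a missing detail. The developer has an interest in the result, and nothing in the article makes that person blind. A recorded interview about functioning can also disclose what treatment the patient received. At stake is how far a GAF-F result could be trusted as a check on a self-reported BAI result. BAI itself is not touched.

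**Working it through.** **1. Who is blinded, read across sections.**
- Blinding: the research team is blinded. GPs, the delivering Collabri team, administrative staff and patients are not. Developers are not mentioned.
- Background: developers were GPs, psychiatrists and researchers. GPs are listed as unblinded, and the delivering team includes psychiatrists (section on the multi-professional Collabri team). Researchers may belong to the blinded team. A developer could therefore be on either side.
- The rule in Blinding that another assistant takes over applies when allocation is revealed to a research assistant before an assessment. It does not cover a developer, or disclosure within a recording reviewed afterwards by several raters.

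**2. What happens to a score after discussion.** The article does not say whether the first rating stands or is replaced.

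**3. When the discussions occur.** The discrepancy sentence covers training and the assessment period. It applies to GAF-F and PSP because it follows a sentence on both eligibility interviews and interviewer-rated assessments, but it is not confined to them.

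**4. The plan's own figure for GAF-F.** Inputs from Table 1 and Power and sample size calculation: difference 5, SD 11, 182 per arm, two-sided 5%.
- SE = 11 × √(2/182) = 1.15. Power = Φ(5/1.15 − 1.96) ≈ 0.991, which reproduces the stated 99%.
- With ICC 0.04 and 48 clusters (Feasibility), the design effect is 1 + (364/48 − 1) × 0.04 = 1.263, SE = 1.15 × √1.263 = 1.30, and power is 0.971.

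The stated power is not in dispute. The SE is needed for step 5.

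**5. Illustration of sensitivity (bias sizes are assumptions).** If a share s of one arm's ratings moved by 5 points in one direction, the contrast would move by 5s. At s = 10% (about 18 of 182 patients) that is 0.5 points, a tenth of the difference in Table 1. With no true effect and a differential shift b, the two-sided error is 1 − Φ(1.96 − b/SE) + Φ(−1.96 − b/SE):

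| Assumed shift b | SE 1.15 | SE 1.30 (clustered) |
|---|---|---|
| 0.5 | 7% | 7% |
| 1 | 14% | 12% |
| 2 | 41% | 34% |

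The article gives neither the share of interviews rated twice nor the share found discrepant, so no row can be called likely.

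**6. What could still be changed.** Recruitment ended on 31 December 2016, so 6-month ratings were due by about the end of June 2017 and 15-month ratings by about the end of March 2018. The article appeared on 16 August 2017. On schedule, only later 15-month ratings were still open.

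**The case against.** The strongest reply is that the concern leans on silence. Locking of scores, handling of consensus ratings and attendance at meetings are matters that an article can leave to the full protocol or a rater manual. The developer may well be a member of the blinded research team. Unblinded parties are told not to disclose allocation to the research team, and a research assistant who learns the arm before an assessment is replaced. Much of this stands, and it limits the point to a gap. It does not remove it, because the developer's part in the discussions is written into the article and those safeguards do not reach the developer.

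A reader might infer more, and the document does not support it:
- **That GAF-F was rated unblinded, or that scores were altered in favour of Collabri.** Nothing says that the developer knows allocation or that a discussed score replaces the first one.
- **That recalibration of raters by an interested party biases the contrast even if scores are kept.** Raters who are blind cannot apply a general recalibration by arm. It would probably act on both arms alike.
- **That the number of discussions is known.** November 2014 to March 2018 is about 40 months, or roughly 13 quarterly rounds. That count includes the initial meeting phase and months with baseline ratings only, since 6-month follow-up could not start before about May 2015.
- **That a main objective is lost.** The stated aim and null hypothesis concern anxiety symptoms. Functioning is a secondary outcome, and PSP is explorative.

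**Conclusion.** The point holds as an unclosed blinding gap on one secondary outcome (GAF-F) and one explorative outcome (PSP). The article involves an intervention developer in discussing rating discrepancies during the assessment period, does not count developers among the blinded, and still presents GAF-F as assessor-blinded. A differential effect needs two conditions that the article does not state: the developer knows or infers the arm, and the discussion changes trial scores. To bias the contrast, those changes would also have to favour one arm. Its size cannot be derived from the documents; the 0.5-point shift and the error rates above rest on assumed inputs. The point is worth acting on because the remedy is cheap and protects the only interviewer-rated outcome among the primary and secondary ones.

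**What to change.** - State that each rater's independent GAF-F and PSP score is locked before any reliability discussion, and that the locked score is the one analysed.
- For the assessments still to come, confine discussion of trial recordings to blinded research staff who neither developed nor delivered Collabri.
- In the trial report, give the blinding status of any developer who took part in earlier rounds.

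A rule limiting developers to training before the trial would have come too late by August 2017, so the second item can apply only from then on. The cost is a sentence or two and a change in who attends existing meetings, with no extra staff or patients. The small downside is less developer input when raters disagree.
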